### Participants

#### Recruitment

The participants will be recruited from the orthopaedic wards of a 1700-bed, tertiary-level, university teaching hospital in Shanghai, China. Recruitment flyers that contain the researcher’s telephone number will be distributed in the wards. Patients who are interested in the study can contact the researcher (QW) by making a telephone call. The researcher will explain the study and provide the participant information statement. Patients will have 2 days to consider whether to participate in this study. If the patients agree to participate, they will sign the consent form, complete the sociodemographic sheet, complete the baseline assessment and be assigned to either the experimental or control group. We expect that 75% of patients are eligible and 56% of eligible patients will consent to participate in the research [20]. It will take approximately 17 weeks to recruit the required number of participants.

#### Inclusion criteria

The inclusion criteria are (1) adults (greater than or equal to 18 years) after unilateral primary THA or TKA, (2) possess a mobile device (e.g., smartphone or tablet) with an Internet connection, (3) able to access the mobile app WeChat, (4) able to complete the programme and relevant follow-up 3 months after hospital discharge, (5) able to communicate with the researcher in Chinese (Mandarin) and (6) able to provide informed valid consent to participate in the study.

#### Exclusion criteria

Participants will be excluded if they (1) undergo revision and bilateral arthroplasty; (2) have concomitant health conditions that might have interfered with the rehabilitation exercises, such as class II or above heart failure according to the New York Heart Association [46]; (3) received other lower-limb surgery in the last 6 months or will undertake another lower limb surgery within 3 months; (4) have severe vision impairment or blindness according to the International Classification of Disease 11 [47]; and (5) have major postoperative complications, such as incision infection and venous thromboembolism.

### Interventions

Interventions will commence immediately after hospital discharge. The experimental group will receive a mobile app rehabilitation programme on top of usual care, whereas the control group will receive usual care only.

#### Usual care

Usual care of the hospital is based on an expert consensus on enhanced recovery after THA and TKA in China [48]. Home-based rehabilitation exercises are explained to the patients by ward nurses at hospital discharge. Take-home rehabilitation instruction pamphlets are also provided. The home-based rehabilitation exercises consist of 12 exercises for THA and TKA, which aim to improve muscle strength, joint mobility and physical function in daily living. Patients are required to practise rehabilitation exercises according to the instructions for 6 weeks. If they have any questions during rehabilitation, they can telephone the ward nurses. Patients will be followed up when they complete the rehabilitation programme (i.e., 6 weeks after hospital discharge) and 4 weeks later (i.e., 10 weeks after hospital discharge).

#### Mobile app rehabilitation programme

The mobile app rehabilitation is a 6-week programme delivered via the mobile app WeChat, which aims to enhance patients’ self-efficacy for rehabilitation as well as improve their outcomes regarding physical function, pain, depression, anxiety and HRQoL. The design of this programme is guided by two theories, Bandura’s self-efficacy theory [49] and Illeris’ model of learning [50]. The exercise regime used in the mobile app rehabilitation programme is the same as that used in usual care to ensure comparability between the groups. The setting of progressive rehabilitation goals and exercise intensities is based on recent literature [51] and an expert consensus on best practices after hip and knee arthroplasty [11].

Both theories adopted in the present study have been recommended in telehealth research because they may facilitate the creation of effective and interactive interventions [52, 53]. Bandura’s self-efficacy theory guides researchers to adopt strategies that may enhance patients’ confidence in their capability to accomplish rehabilitation tasks. According to the theory, there are four sources of self-efficacy: direct mastery experiences, vicarious experiences, verbal persuasion and arousal state [49]. The present study addresses these four sources with the establishment of achievable small goals as well as the provision of peer sharing, a discussion forum and psychological techniques [31, 54]. Illeris’ model of learning guides researchers to understand the nature of the learning process and the conditions that influence this process [50]. To facilitate the participants’ learning process, the present study uses visual presentations, such as pictures and videos, rather than text messages, and the information is delivered in short segments.

The mobile app rehabilitation programme consists of physical exercises as well as techniques for enhancing participants’ self-efficacy for rehabilitation. The exercises incorporated in the mobile app rehabilitation programme are similar to usual care, and they are demonstrated by videos or photos via WeChat. Participants are encouraged to practise the exercises for 1 h daily and at least 5 days per week [20, 22, 55]. Exercise goals for each week are established, and rehabilitation instructions are arranged in small tasks to help participants achieve the overall exercise goals. Previous patients who have completed the rehabilitation and recovered are invited to share their experiences via the app. An asynchronous discussion forum will be held via WeChat, involving all participants in the experimental group, the researchers, an arthroplasty surgeon, a nurse and a physiotherapist. Participants can post their experiences and questions at any time. The researcher (QW) will respond to the questions within 24 h. Praise, encouragement and reassurance will be provided through discussions and chats. To help relieve stress and anxiety, techniques, such as muscle relaxation exercises, are included in this programme. More details are provided in Additional file 2. The mobile app rehabilitation programme has been reviewed for content validity by a panel that consisted of an arthroplasty surgeon, a nurse, a physiotherapist and two patients.

The mobile app rehabilitation programme will be delivered by the researcher (QW). On the day before hospital discharge, the researcher will teach the participants in the experimental group to use the programme on WeChat. A booklet that illustrates how to use the mobile app rehabilitation programme will also be provided to take home. To improve engagement, the researcher will send a message on Monday of each week to remind the participants to undertake exercises, and the participants will be encouraged to record their use of the programme and completion of the rehabilitation tasks in a paper diary.

#### Concomitant rehabilitation and medications

At the orthopaedic surgeon’s request, some participants may undertake additional in-person rehabilitation sessions during the programme. These participants will be included in the data analysis, but they will be asked to report this concomitant intervention by answering two additional questions on the outcome assessment questionnaires: ‘Have you been required to attend in-person rehabilitation? If yes, how many times?’ Other regular medications the participants take during the programme will also be collected at baseline.

### Outcome measures

Data will be collected at three time points: at baseline (week 0, T0), at week 6 immediately after the intervention (T1) and at week 10 as follow-up (T2). Demographic data, including age, gender, living status and education as well as a brief history of health conditions, including surgery, comorbidities and medication, will be collected at T0. The following outcomes will be measured at T0, T1 and T2. Both the experimental and control groups will be assessed by the same assessor using the same measurements and following the same time frame. The assessor will assess the participants via telephone if they are unable to attend the hospital for face-to-face assessment at T1 and T2. The SPIRIT schematic diagram is presented in Fig. 2.

**Fig. 2 Fig2:**
[figure not shown]
Study schedule of enrolment, interventions and assessments

After being recruited, the participants will complete the baseline assessment and then be randomly allocated to either the experimental or the control group. The experimental group will receive a mobile app rehabilitation programme on top of usual care, whereas the control group will receive usual care only. The interventions will last 6 weeks. All outcome measures will be conducted at baseline, completion of the intervention (week 6) and follow-up (week 10). SER Self-Efficacy for Rehabilitation Outcome Scale, HOOS-PS Hip Disability and Osteoarthritis Outcome Score Physical Function Short Form, KOOS-PS Knee Injury and Osteoarthritis Outcome Score Physical Function Short Form, NRS Numeric Rating Scale and HADS Hospital Anxiety and Depression Scale.

#### Primary outcomes

The primary outcomes are changes from baseline in self-efficacy and physical function at the completion of the intervention (T1). The intervention is based on the self-efficacy theory, aiming to improve patients’ physical function after surgery. These two outcomes may provide the most relevant and convincing evidence related to the aim of this study. The study results will be considered positive only if the intervention has an effect on both primary outcomes; thus, no adjustment for multiplicity will be conducted in data analysis [56].

Patients’ self-efficacy for rehabilitation will be measured using the Chinese version of the Self-Efficacy for Rehabilitation Outcome Scale (SER) [57]. The SER is sufficiently reliable and valid to detect patients’ self-efficacy for rehabilitation after hip or knee reconstructive/replacement surgeries [58]. It consists of 12 items that assess individuals’ beliefs in their ability to perform behaviours typical of physical rehabilitation, and each item is rated on an 11-point Likert scale from 0 indicating ‘I cannot do it’ to 10 indicating ‘certain I can do it’ [59]. Higher scores indicate greater self-efficacy.

Patients’ physical function will be measured using the Chinese version of the Hip Disability and Osteoarthritis Outcome Score Physical Function Short Form (HOOS-PS) for patients after THA and the Knee Injury and Osteoarthritis Outcome Score Physical Function Short Form (KOOS-PS) for patients after TKA [60, 61]. The HOOS-PS and KOOS-PS are valid for assessing patients’ perceptions of their hip or knee functions [62]. The HOOS-PS has five items, whereas the KOOS-PS has seven. Each item is graded from 0 indicating ‘no difficulty’ to 4 indicating ‘extreme difficulty’ [60, 61]. The raw sum score can be further converted in two directions: from no difficulty (0) to extreme difficulty (100) or from extreme difficulty (0) to no difficulty (100) [63]. To align with other scales in this study, such as the SER and EQ-5D-5L, the scores will be summed using the nomogram of worst (0) to best (100), with higher scores indicating better physical function. The minimal clinically important difference used in this study is 8 points for the HOOS-PS or KOOS-PS [64].

#### Secondary outcomes

The secondary outcomes are changes from baseline in pain, anxiety, depression and HRQoL at T1 and T2, as well as changes from baseline in self-efficacy and physical function at T2. Adherence-related data will also be collected as supportive secondary outcomes.

Patients’ perceived level of pain will be measured using the Numeric Rating Scale (NRS) [65]. This study will use a horizontal 11-point numerical scale, with 0 representing ‘no pain at all’ and 10 representing ‘pain as bad as it could be’. Participants could select a number (0–10 integers) to reflect the intensity of their pain. The NRS is reliable (*r* = 0.96) with good construct validity (*r* = 0.95 correlated to the visual analogue scale), and it is preferred by the patients with pain over other measures because it is easy to comprehend and complete [65]. To maintain consistency in pain assessment, the NRS will be included in the paper diary, and the participants will mark their pain level daily when they wake.

Patients’ levels of anxiety and depression will be measured using the Chinese version of the Hospital Anxiety and Depression Scale (HADS) [66]. The HADS is a widely used instrument to measure the severity of anxiety and depression among patients in nonpsychiatric clinics [67]. It is a 14-item instrument containing two subscales: anxiety (HADS-A, 7 items) and depression (HADS-D, 7 items). Each item is scored using a 4-point Likert scale ranging from 0 indicating ‘not a problem’ to 3 indicating a ‘high level of problems’ [66]. The subscale scores of the HADS-A and HADS-D can be obtained by summing of individual item scores.

Patients’ perceived HRQoL will be measured using the Chinese version of the EQ-5D-5L [68]. The EQ-5D-5L measures HRQoL on five dimensions: mobility, self-care, usual activities, pain/discomfort and anxiety/depression [69, 70]. In each dimension, respondents can indicate their health by ticking the box next to the most appropriate statement, and a digit number expressing the level selected will be produced [68]. Combining the digits for each dimension will produce a five-digit code that describes the patient’s health state. To compare the health state between the groups, the codes will be converted to index values according to the established value set for China [71]. The participants’ judgement of their health will be recorded with the EQ-VAS, where the endpoints are marked as 100 indicating ‘the best health you can imagine’ and 0 indicating ‘the worst health you can imagine’ [68].

The number of days when the participants use the WeChat programme and complete their rehabilitation tasks will be collected through reviewing rehabilitation diaries. The frequency of participants’ posts in the discussion forum on WeChat will be counted to understand online engagement. Complications and fall incidence that occur after randomisation will be investigated by additional questions on the questionnaire to provide information about the safety of using the app. With the individual’s consent, an interview will be conducted to discuss the benefits and barriers to using the app with participants in the experimental group.

### Data analysis plan

IBM® SPSS Statistics 26.0 will be used to analyse the data [72]. The first author will perform data entry and analysis using participants’ identification codes. Categorical variables, such as gender, will be presented in frequencies and percentages. Continuous variables, such as age, will be presented as means with standard deviations or medians with interquartile ranges. Demographic characteristics and baseline variables will be compared between the two groups. Student’s *t*-tests will be used if the continuous data are normally distributed; otherwise, Wilcoxon rank-sum tests will be used. For categorical data, chi-square tests or Fisher exact tests will be conducted when chi-square testing is not valid. The effectiveness of the intervention will be analysed using the intention-to-treat principle [73]. The generalised estimating equation (GEE) model [74] will be used to compare the differential changes in the outcome variables between the groups across time points at a significance level of 0.05 (two-tailed). The GEE increases the efficiency of the estimates of the parameters in longitudinal trials by accounting for the within-subject correlations in repeated measurements [75]. This model is flexible to use as it relaxes the distribution assumptions of observed data and can accommodate missing data due to dropouts in RCTs [75, 76]. No imputation will be conducted if the proportion of missing data is less than 5% as the GEE can naturally integrate the missing data; otherwise, multiple imputations may be conducted [77].

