## Methods/design

### Study design

This is a single-centre, single-blinded, superiority RCT with two parallel groups. Participants undergoing primary THA or TKA will be recruited preoperatively in the orthopaedic wards. They will receive standard inpatient rehabilitation services and the same care during hospitalisation. On the day before hospital discharge, they will complete the baseline assessment (T0) and will be randomly assigned to the experimental or control group. Once discharged, the experimental group will receive a 6-week mobile app rehabilitation programme and usual care, whereas the control group will receive usual care for 6 weeks. Outcomes will be assessed at 6 weeks (T1) and 10 weeks (T2) after hospital discharge. The flowchart of the RCT is presented in Fig. 1. The Standard Protocol Items: Recommendations for Interventional Trials (SPIRIT) checklist is provided in Additional file 1.

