#### Sample size

The sample size was calculated using the formula developed by Sugimoto et al. [42], incorporating the co-primary outcomes of this study: physical function and self-efficacy. Based on previous studies in arthroplasty, we expect the effect size of the intervention on self-efficacy to be 1.2 and that on the physical function to be 0.7 [20, 43]. The effect size ratio is approximately 1.7 (1.2/0.7). The correlation coefficient between these two outcomes was estimated to be 0.3 [44]. We set the attrition or nonresponse rate at 20% based on the evidence from the study of Walters et al. [45]. The present study requires a sample size of 84 in all (42 in each group) to achieve a power of 0.8 at a 0.025 level of alpha error.

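### The co-primary comparison of change from baseline names no adjustment for the T0 score, so the T1 contrast is likely to be less precise than it could be

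*Protocol article*

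**What the plan says.** Primary outcomes: "The primary outcomes are changes from baseline in self-efficacy and physical function at the completion of the intervention (T1". Both must show an effect for the trial to count as positive. Secondary outcomes places the T2 changes in the same two measures among the secondary outcomes.

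Study design: "On the day before hospital discharge, they will complete the baseline assessment (T0", with assignment afterwards. The Randomisation section confirms this order and specifies simple 1:1 randomisation.

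Data analysis plan: the GEE "will be used to compare the differential changes in the outcome variables between the groups across time points". The same sentence sets the test level: "at a significance level of 0.05 (two-tailed". The method is justified by its handling of correlation within patients. No baseline covariate is named. The one stated use of baseline values is to test for differences between the groups. The model terms are not listed.

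Sample size: "we expect the effect size of the intervention on self-efficacy to be 1.2 and that on the physical function to be 0.7", and "The correlation coefficient between these two outcomes was estimated to be 0.3". That last figure links the two outcomes with each other, not T0 with T1. The total of 84 includes 20% attrition and is said "to achieve a power of 0.8 at a 0.025 level of alpha error".

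**The concern.** T0 is measured before assignment, so any group difference at T0 is due to chance. A model that leaves this difference free, and subtracts it in full from the T1 difference, carries all the noise of the T0 measurement into the treatment contrast. Adjusting for the T0 score subtracts only the part that predicts T1. When T0 predicts T1 weakly, the gap between the two is large. T0 is taken in hospital soon after surgery, so a modest correlation with week 6 is plausible, but the article gives no figure.

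The stakes are higher than usual for two reasons. The sample size has almost no slack, and both co-primary outcomes must succeed, so imprecision on physical function, the smaller effect, bears directly on the chance of a positive trial.

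**Working it through.** **1. Reproduce the plan's figure.** Inputs from the Sample size section: effects 1.2 and 0.7, correlation between outcomes 0.3, alpha 0.025, power 0.8, attrition 20%. Joint power with n evaluable per arm is the bivariate normal probability (correlation 0.3) that both statistics, with means d√(n/2), exceed 1.96. With n = 33, √(33/2) = 4.062:
- physical function: 0.7 × 4.062 − 1.96 = 0.88, power 0.81;
- self-efficacy: 1.2 × 4.062 − 1.96 = 2.91, power above 0.99;
- joint power 0.811.

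Then 33/0.8 = 41.25, so 42 per arm and 84 in all, an exact match. It needs alpha 0.025 read as one-sided, which agrees with the two-tailed 0.05 of the analysis. Two-sided 0.025 would give 98.

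**2. What the planned contrast estimates.** A simulated GEE with time, group and their interaction, all three visits as outcomes and exchangeable working correlation, returned on complete data exactly the difference in mean change at T1.

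**3. Relative precision.** Take the T1 SD as 1 and assume the T0 SD is equal to it:
- variance of change: 2(1 − r);
- variance after adjustment for T0: 1 − r²;
- ratio: 2(1 − r)/(1 − r²) = 2/(1 + r).

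The adjusted confidence interval is narrower by 1 − √((1 + r)/2).

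| r (assumed) | change | adjusted | ratio | CI narrower by |
|---|---|---|---|---|
| 0.3 | 1.40 | 0.91 | 1.54 | 19% |
| 0.5 | 1.00 | 0.75 | 1.33 | 13% |
| 0.7 | 0.60 | 0.51 | 1.18 | 8% |

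**4. Unequal SDs.** With k = T0 SD / T1 SD, the variance of change is 1 + k² − 2kr. The excess over the adjusted variance is (1 + k² − 2kr) − (1 − r²) = (k − r)², which is never negative. At an illustrative k = 0.7:
- r = 0.3: 1.07 against 0.91, CI 8% narrower;
- r = 0.5: 0.79 against 0.75, CI 3% narrower.

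A k above 1 widens the gap.

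**5. Joint power with 33 per arm.** Equal SDs; correlation between outcomes held at 0.3. The article does not say which SD standardises 1.2 and 0.7, so both readings are shown.

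| r | T1-score SDs: change | T1-score SDs: adjusted | change SDs: change | change SDs: adjusted |
|---|---|---|---|---|
| 0.2 | 60% | 83% | 81% | 96% |
| 0.3 | 67% | 85% | 81% | 94% |
| 0.4 | 74% | 87% | 81% | 93% |
| 0.5 | 81% | 91% | 81% | 91% |
| 0.7 | 96% | 98% | 81% | 87% |

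Example, T1-score SDs at r = 0.3, physical function: 0.7/√1.40 = 0.592 for change, and 0.592 × 4.062 − 1.96 = 0.44, power 0.67. Adjusted, 0.7/√0.91 = 0.734, and 0.734 × 4.062 − 1.96 = 1.02, power 0.85. Self-efficacy barely lowers the joint figure.

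**The case against.** The article lists no model terms. It does not state that T0 is an outcome row, that the T0 means are unconstrained, or that adjustment is excluded, and a condensed article may leave covariates to the full protocol. A change-from-baseline endpoint is also compatible with baseline adjustment. This stands as a limit: the model examined here is the natural reading, not a quoted specification. It does not remove the point, because the text commits to comparing changes and gives T0 no other role in the effect estimate.

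The difference in change is unbiased under randomisation and does not inflate type I error. That also stands; the issue is efficiency only.

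A reader might infer that the trial is underpowered. The documents do not support this. The shortfall needs both r below 0.5 and effect sizes in T1-score SDs. Since the co-primary outcomes are themselves changes, change-score SDs are at least as natural a reading, and on that reading the planned power is kept at every r.

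A reader might also infer from the reference to several time points that the primary test is a joint interaction test that T2 could drive. No such test is mentioned, and the outcome sections already make T1 primary and T2 secondary.

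**Conclusion.** The point holds as an efficiency recommendation. On the natural reading of the plan, the T1 contrast has 1.18 to 1.54 times the variance of a baseline-adjusted contrast for r from 0.7 to 0.3. That rests on equal SDs at T0 and T1, complete data and assumed values of r. The loss is smaller if the T0 SD is moderately below the T1 SD, and larger if it is above. With the planned 20% attrition, the identity with the raw difference in change need not be exact.

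The sample size is right on its own inputs. Whether the stated 80% is at risk cannot be settled from the article. On one reading of the effect sizes only additional power is forgone; on the other, power drops below 80% when r is under 0.5. Adjustment has the higher power on both readings at every r shown.

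**What to change.** Before outcome data are examined, prespecify for each co-primary outcome a one-degree-of-freedom group contrast at T1, adjusted for the T0 score. Either of two models will do:
- T1 and T2 scores as outcomes, with T0 score, T0 by time, group, time and group by time as terms;
- all three visits as outcomes, with group means constrained equal at T0. This form needs a working correlation other than independence, under which the T0 values would not contribute to the T1 contrast.

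Keep the T2 contrasts secondary, as the article already has them. State which SD the effect sizes 1.2 and 0.7 refer to, and the T0–T1 correlation assumed.

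The estimand, the between-group difference in change at T1, is unchanged, and the T0 scores are already collected. The cost is procedural. Under Modification of the protocol, a change to the data analysis that may affect conduct or ethical rigour is substantive: it needs a formal written modification, approval by the ethics committees of the university and the study venue, a register update and notification of participants, with consent to the modified study. The article reports 48 participants already recruited, so these steps would apply to people in the trial.

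### At the 20% attrition the trial plans for, the protocol leaves multiple imputation of the co-primary outcomes optional, and it justifies unweighted GEE by a claim that is not generally true

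*Protocol article*

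**What the plan says.** All of the following is in the Protocol article.

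- **Data analysis plan, principle and model.** "The effectiveness of the intervention will be analysed using the intention-to-treat principle". A GEE model compares change between groups across the visits, "at a significance level of 0.05 (two-tailed").
- **Data analysis plan, rationale.** The model is chosen partly because it "can accommodate missing data due to dropouts in RCTs".
- **Data analysis plan, rule below 5% missing.** "No imputation will be conducted if the proportion of missing data is less than 5% as the GEE can naturally integrate the missing data".
- **Data analysis plan, rule at 5% or more.** "otherwise, multiple imputations may be conducted". This is the only rule for that case.
- **Sample size.** "We set the attrition or nonresponse rate at 20"%, which is built into the 84 participants.
- **Primary outcomes.** Self-efficacy and physical function at T1 must both show an effect for the trial to be positive.

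The article states no missing-data assumption, weighting or working correlation for the GEE.

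**The concern.** There are two linked faults, and both lie in what the text states.

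First, the rationale. GEE will run on whatever visits are available, but that does not make the estimate valid. Without weighting, consistency is guaranteed only when data are missing completely at random, or when missingness depends only on covariates in the model. Dropout that depends on a patient's earlier scores falls outside that guarantee.

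Second, the rule. The firm part (no imputation) covers a case the trial does not plan for. The part that covers the planned attrition is permissive. GEE with and without imputation can give different answers on the same data. The Blinding section names only the outcome assessor as blinded, and the Data analysis plan has the first author enter and analyse the data. A choice left until the data are in hand is therefore a real opening for selection on both co-primary outcomes.

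Outcome-related missingness is plausible here. Under Ethical consideration, a participant's involvement may end after events such as dislocation or a severe fall, and these bear directly on physical function.

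**Working it through.** **1. Is 20% really built into the design?** Inputs from the Sample size section: "we expect the effect size of the intervention on self-efficacy to be 1.2 and that on the physical function to be 0.7"; correlation 0.3; "to achieve a power of 0.8 at a 0.025 level of alpha error". Read alpha as one-sided 0.025, which equals two-sided 0.05. With n per arm, the two test statistics have means 0.7 × √(n/2) and 1.2 × √(n/2), with correlation 0.3. Joint power is the probability that both exceed 1.96.

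- n = 32: means 2.80 and 4.80, joint power 0.799.
- n = 33: means 2.84 and 4.87, joint power 0.811, so 33 per arm.
- Allowing for 20% loss: 33 / 0.8 = 41.25, so 42 per arm and 84 in all.

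The stated figure is reproduced. (Two-sided 0.025 would give 39, inflated to 49 per arm, which does not match.)

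**2. Which branch should the trial expect?** 5% of 84 is 4.2, so the under-5% rule needs at most 4 participants missing. At 20% the expected number is 0.20 × 84 = 16.8. The binomial probability of 4 or fewer out of 84 at 20% is 0.00007. Counting records rather than participants gives the same branch. With T0 complete and 20% missing at T1 and T2, the share is 2/3 × 20% = 13.3%. If the loss is at T2 only, it is 1/3 × 20% = 6.7%.

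**3. How large could the bias be?** The documents give no dropout mechanism, so these inputs are assumptions: no true effect; 20% dropout before T1 in each arm; log-odds of dropout changing by 1 per SD of the T0 score; T0-T1 correlation r of 0.3, 0.5 or 0.7; normal outcomes.

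Under an independence working correlation, the T1 mean in each arm is simply the completers' mean. With this mechanism the completers' mean T0 score shifts by 0.173 SD, so their T1 mean shifts by 0.173 × r.

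| Dropout dependence | r = 0.3 | r = 0.5 | r = 0.7 |
|---|---|---|---|
| One arm only: 0.173 × r | 0.05 | 0.09 | 0.12 |
| Opposite directions: 2 × 0.173 × r | 0.10 | 0.17 | 0.24 |
| Same in both arms | 0 | 0 | 0 |

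Simulations with up to 400,000 patients per arm agree, giving 0.05-0.13 SD (one arm) and 0.10-0.25 SD (opposite). The largest value is 0.25 / 0.7, or about 35% of the planned effect on physical function.

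**4. Same mechanisms, other working correlations.** When an exchangeable or unstructured working correlation fits the data, simulated bias was about 0.02 SD or less. With an exchangeable structure fitted to autoregressive data it was at most 0.03 SD.

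**5. Type I error at N = 84** (r = 0.5-0.7, nominal 0.05, 1,500 simulated trials per setting):

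- Independence, one arm only: 0.07-0.10.
- Independence, opposite directions: 0.11-0.21.
- Exchangeable or unstructured: about 0.06.

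**The case against.** The strongest reply is that the larger bias figures need two things the document does not state.

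- **Working correlation.** Independence is not named. The plan's own argument for GEE, efficiency from using the within-subject correlation, fits independence poorly. With an exchangeable structure the bias nearly vanishes. The choice of structure may also properly sit in an analysis plan that is not shown, so its absence is not a fault. This stands, and it is why the independence figures are only the unfavourable end of a range.
- **Mechanism.** Nothing in the documents shows dropout selecting in opposite directions by arm. Dislocation or a fall can happen in either arm, and equal dependence in both arms gives no bias. The Background reports poor adherence to unsupported home exercise, but adherence is not attrition. This stands too.

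Further, the 20% is a sample-size allowance taken from a cited source, not a forecast, and telephone assessment at T1 and T2 (Outcome measures) should reduce loss. That is fair, but it is the only attrition figure the protocol gives, and the missing-data rule should work at it. Below 5% missing, skipping imputation matters little: with 5% dropout, even opposite dependence under independence gives only 0.03-0.07 SD.

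A reader might also infer that the standard errors are too small for about 33 completers per arm. The documents do not support that, because no variance estimator is named.

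None of this removes the optional wording or makes the stated rationale correct.

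**Conclusion.** The point holds as a should-fix. The protocol's own planning figure puts the co-primary analysis in the branch where imputation is permitted but not decided, and the stated reason for relying on GEE is not true in general. That conclusion needs only the 20% and 5% figures and the optional wording.

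The size of any bias is conditional. It ranges from nil (equal dependence in both arms), through about 0-0.03 SD (exchangeable working correlation), to 0.05-0.12 SD (one arm) and 0.10-0.25 SD (opposite directions) under independence. All of these assume the dropout strength and correlations set out above.

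A reader might infer that the planned GEE will give a biased week-6 effect, or that dropout is likely to differ by arm. The documents establish neither. What they show is that the protocol commits to nothing that would protect against it.

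**What to change.** In the Data analysis plan:

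1. Delete the claim that GEE deals with missing data by itself, and state the assumption on which the primary analysis rests: missing at random given the observed data.
2. Replace the 5% threshold and the optional wording with one primary method, fixed before the data are seen and valid under that assumption. Either of these would do:
   - GEE after multiple imputation carried out by arm, using T0, T1 and T2. Multiple imputation is already named in the plan.
   - A likelihood-based repeated-measures mixed model on all observed data.
3. Optionally, add a delta-adjusted sensitivity analysis for the two co-primary outcomes.

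The cost is a wording change and a little more programming. The mixed model or the imputation model brings an approximate normality assumption for the scale scores. The sample size stays at 84 and nothing changes for participants. The section on modification of the protocol already provides the route for amending the data analysis.
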